## Abstract

**Background:** Cancer patients are now facing a double distinctive challenge of survival against both the disease and fear of contracting COVID-19. This challenge has resulted in the forced adoption of social distancing measures and reorganization of the delivery of medical and psychological treatments. The perceived loneliness and uncertainty increased distress and symptoms burden. In the current period, eHealth interventions might provide valuable benefits in the field of cancer care.

**Objective:** The overall goal of the study protocol will be to provide an innovative intervention for cancer patients based on an online platform, to help them manage and prevent psychological problems related to social isolation. Specifically, the efficacy of two web-based interventions aimed at lowering stress in cancer patients will be tested and compared.

**Methods:** One hundred and fifty participants (75 per group) will be enrolled in a two-group randomized trial. The two interventions will be composed either by exercises on relaxation and meditation practices, presented in both automated online content and interactive group sessions or by fixed psychoeducational online content. Stress, anxiety, and depressive symptoms, distress, resilience, and perceived social isolation will be measured before the start of the interventions (T0), 2 weeks (T1), 4 weeks (T2), and 2 months (T3) after the beginning of the interventions in both groups. A repeated measures ANOVA will be performed to test differences in the questionnaires' scores between groups across the four-time points.

**Expected Results:** We hypothesized greater improvement in the specific domain of stress symptoms (IES-R) assessed in the group receiving the interactive intervention, compared to the group which will receive only fully automated psychoeducational content. Secondarily, we expect the same trend of improvement across all the psychological variables in the blended intervention group.

**Conclusions:** Implementing these practices on people who are forced into mandatory social isolation may help them become more aware of their mind-body condition and reduce negative effects. Moreover, relaxation techniques help individuals in achieving a greater state of well-being, increasing the ability to cope with stressful situations (resilience), and strengthening the immune system.

## Introduction

The COVID-19 pandemic has spread worldwide. It has been 1 year since Italy has forced a strict lockdown, with a drastic reorganization of the healthcare system. To contain the extensive viral spread, hospitals are implementing several measures to cope with the demand for care and adequately address patients' needs (van de Haar et al., 2020). The risk of exceeding healthcare systems' capacity has led to the adoption of social distancing measures and the reorganization of medical treatment delivery. Further restrictions were adopted in hospitals such as limiting elective surgical interventions, restricting caregivers' visits during hospital stays, reducing systemic treatment intensity, and improving teleconsultations (Sigorski et al., 2020). This is even more difficult with people with a higher risk of getting infected. In particular, the scientific studies showed that patients with cancer were more vulnerable to both the SARS-CoV-2 infection and its complications (Emami et al., 2020).

Cancer patients are facing a double distinctive challenge of survival against both the disease and fear of contracting the virus. The perception of physical vulnerability to the illness enhanced arousal and triggered the anxiety. Patients are overwhelmed by conflicting advice and fear of cancer recurrence (Miaskowski et al., 2020). The lack of social connections may enhance patients' feelings of loneliness and uncertainty and they may contribute to the exacerbation of distress and symptom burden, with a higher risk of mortality (D'ippolito et al., 2017; Young et al., 2020). A recent study on 6,213 cancer patients showed that 23.4% of them reported depression, 17.7% anxiety, and 9.3% post-traumatic symptoms during the COVID-19 pandemic (Wang et al., 2020; Pigozzi et al., 2021). Moreover, another study analyzing the psychological burden of cancer patients before and after the pandemic highlighted higher levels of stress compared to non-cancer patients (Miaskowski et al., 2020). On the other hand, resilience has been described as a protective factor in life-threatening events and it plays a crucial role in determining how individuals react to and deal with stress. Resilience may be defined as the individual's ability to have biological, mental, and spiritual balance in the face of hazardous conditions, such as cancer and/or pandemics (Seiler and Jenewein, 2019). Moreover, patients often reported widespread concern and psychophysiological reactions related to stressful situations like the COVID-19 pandemic; they may also experience a psychophysiological hyperactivation, thus paying excessive attention to bodily sensations. Finally, hospitalization and management of acute complications of psychological problems increase the direct costs of treatments, while the increased disability may affect overall indirect costs due to the loss of productivity. The psychological burden can exacerbate the medical condition that in turn affects personal costs resulting from the loss of physical independence and the need for a carer, suddenly becoming a social cost (e.g. hospitalization, surgical and medical management, and institutionalization) (Sporinova et al., 2019).

Starting from these premises, there is an urgent need to address the enormous psychological burden of COVID-19 on those affected by cancer, while allowing the necessary social distancing. In this context, in-person participation was rapidly curtailed by the implementation of remote interventions able to facilitate stress management and enhance physical and emotional well-being (Trevino et al., 2021). Currently, in the field of eHealth treatments, the use of blended care is gaining visibility. The term “blended” refers to the combination of online and offline elements inside the same care-flow intervention. This “technology-supported” care combines unguided self-help modules with (scripted) face-to-face sessions. Offline and online components are interrelated methods that are strategically combined to build an intervention that merges the potential benefits of the two approaches (Wentzel et al., 2016). To date, the literature demonstrates that blended therapy displays encouraging effects (Wentzel et al., 2016) and can be used to deliver personal or automated feedback and support, synchronous or asynchronous guidance, and it can aid via online guidance or self-help units. The blended treatment could be innovatively provided through the implementation of online and offline relaxation techniques.

In this regard, previous studies demonstrated that interventions based on respiration and meditation helped individuals to alleviate the effects of stress by reducing physiologic arousal and restoring autonomic balance (Ditto et al., 2006; Wielgosz et al., 2019). Guided relaxation techniques can help people to achieve a deep state of relaxation through breathing exercises and focusing attention on body perception (e.g., body scan). The former may also be defined as “an efficient integrative body-mind training for dealing with stress, anxiety, and psychosomatic conditions”; it may help people slow their breathing, take in more oxygen, and reduce the use of shoulder, neck, and upper chest muscles, thus achieving better emotional balance and well-being (Porges, 2001). On the other hand, body scans aim to focus attention on different parts of the body and encourage awareness of the body's sensations, such as pain, tension, warmth, or relaxation. These techniques affect the physiological functions reducing hyperarousal and carry physical and psychological benefits: people learn how to actively modulate their breath and heartbeat, thus lowering anxiety and distress symptoms, and making room for positive thoughts and feelings (Zaccaro et al., 2018).

Forced social isolation will lead to the implementation of these practices using eHealth interventions. The usefulness of eHealth interventions is supported by studies showing that online relaxation interventions led to significant results as well as in-person interventions (Jung et al., 2016). Increasing the use of these therapies may lead to positive health outcomes and improve quality of life by preventing or delaying the onset of complications, reducing healthcare costs, and hospitalizations. The project's overall vision is to cost-effectively enhance relaxation interventions to reduce the effects of social isolation caused by the COVID-19 pandemic at both individual and societal levels and optimize health outcomes. The project will engage, train, and motivate patients by establishing the connection to raise awareness on the side effects of social isolation and improve their expertise on relaxation techniques. Achieving psychological and physical benefits, such as reducing heartbeat and stress activation or improving concentration, mood, and sleep quality are important factors that could be associated with the administration of pharmacological intervention and patient hospitalization. In fact, the use of non-pharmacological interventions, such as relaxation techniques, has been linked to greater clinical outcomes and a decrease in hospital admissions and healthcare costs (Ozamiz-Etxebarria et al., 2020). On the other hand, psychoeducational intervention showed significant results in cancer patients by improving disease care techniques and quality of life, reducing treatment-related discomfort, and lowering psychological burdens, such as distress, depression, and anxiety symptoms (Wu et al., 2018). Furthermore, the psychoeducational approach has been already applied as an active control group in internet-based protocols (Newby et al., 2018).

## Objective and Aims

The overall goal of the study is to provide an innovative intervention for cancer patients based on an on-line platform and help them to manage and prevent psychological problems related to social isolation. Specifically, the aim is to test and compare the efficacy of two web-based interventions (guided relaxation techniques vs. psychoeducational material) aimed at lowering stress in cancer patients.

## Materials and Methods

### Participants and Procedure

Participants will be enrolled through email. Those who will accept to take part in the study will be asked for the signature of the informed written consent. The study will receive ethical approval of the Ethical Committee of the University of the last author of the work. Then, participants will be randomly assigned to one of the two groups. In both groups, participants will receive on their email an invitation for an online platform where they will access the material. Participants will receive weekly reminders via e-mail.

A total of 150 participants (75 per group) will be enrolled based on the following inclusion criteria: (1) cancer patients (illness stage I–II); (2) aged from 18 to 65 years; (3) having an internet connection at home; (4) having a sufficient physical ability (auditory and visual ability) to use a remote internet device; (5) being a proficient Italian speaker; (6) providing the written informed consent. Patients (1) with neurological or psychiatric diseases, (2) hospitalized, and (3) with expertise in relaxation techniques or meditation will be excluded from the study.

Participation in the study will be voluntary, and participants will be allowed to withdraw from the study at any moment. The research protocol follows the CONSORT-EHEALTH V1.6 Guidelines (Eysenbach and CONSORT-EHEALTH Group, 2011). The study will be conducted according to the principles stated in the Declaration of Helsinki (59th WMA General Assembly, World Medical Association, 2008).

### Study Design and Measures

A between-subjects design will be adopted to administer one of two web-based interventions (guided relaxation techniques vs. psychoeducational material) to both cancer patients' groups. The web-based interventions will be composed of exercises on relaxation and meditation practices, presented in both automated content and interactive group sessions, or by fixed psychoeducational content.

In the blended intervention group, participants will be split into three sub-samples of 25 persons, and they will receive twice a week 1 audio of 10 min and a video clip of 15 min, with the guided exercise of relaxation or meditation. Plus, once a week, participants of the blended intervention group will be asked to participate in a 45 min group session with a psychotherapist that will guide some relaxation exercises. We decided to divide the sample into sub-samples of 25 participants to simplify the management of the groups. Indeed, conducting 45 min groups with more participants might lower the possibility of interaction between participants and with the psychotherapist. For example, the psychotherapist might ask for personal sharing of the experience or participants might have the necessity to ask questions.

In the psychoeducational group, participants will receive three times a week a link with psychoeducational content on stress, anxiety, hyperarousal, and social isolation (video, audio, and text). The materials used in the present study will be created *ad hoc* by the two first authors, in collaboration with a trained psychotherapist. A detailed description of the interventions is reported in Appendix A in Supplementary Material.

Along with the sociodemographic variables (age, gender, employment status, marital status, and level of education), all the participants will complete the following validated questionnaires:

the Hospital Anxiety and Depression Scale (HADS) (Zigmond and Snaith, 1983) for assessing anxiety and depressive symptoms. It is a 14-items scale divided into two subscales ranging from 0 (not at all) to 3 (high presence of symptoms), with higher values indicating higher levels of anxiety and/or depression;the Distress Thermometer for measuring distress symptoms (Jacobsen et al., 2005; Donovan et al., 2014). It is a single-item tool with a Likert scale ranging from 0 (no distress) to 10 (extreme distress);the Impact of Event Scale-Revised version (IES-R) (Weiss, 2007) for assessing the reflect intrusion (eight items), avoidance (eight items), and hyperarousal (six items) related to traumatic events. It is a 22-item scale ranging from 0 (not at all) to 4 (extremely), with a higher score indicating higher distress in response to a specific traumatic event;the Connor-Davidson Resilience Scale (Connor and Davidson, 2003) for measuring the resilience level of cancer patients. It contains 25 items ranging from 1 to 5, with higher scores indicating higher resilience;the UCLA Loneliness Scale (Version 3) (Russell, 1996) for assessing social loneliness. It consists of 20-items ranging from 1 (Never) to 4 (Often), with a higher score indicating greater feelings of loneliness and social isolation.

All the previous questionnaires will be administered before the start of the interventions (T0). Two weeks (T1), 4 weeks (T2), and 2 months (T3) after the beginning of the interventions, participants will be asked to complete the same questionnaires.

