### Sample Size Calculation and Statistical Analysis

We computed the required sample size with the G^*^Power 3.1.9.2 software (Faul et al., 2007; Erdfelder et al., 2009) for the *F*-test. The main endpoint will be the difference in the improvement of the overall score of the IES-R scale. A repeated measure ANOVA will be performed to test differences in the IES-R total scores between groups across the four-time points. The Type I error (α) rate was set at 0.05 (two-sided) and the Power (1 – β) was set at 0.95. The a priori correlation between repeated measures was set at 0.5 and the value of the F was set at 0.25 (*medium* effect size). We found a required sample of 132 subjects. To consider the possibility of attrition, we increased the sample by 14% of the required sample size. The total sample resulted in 150 participants (75 per group). Time will be considered a within-subjects variable, while the type of intervention will be considered a between-subject variable. *Post hoc* comparisons with the Tukey HSD-test will be performed and the effect sizes will be reported in the form of η^2^.

The same analyses will be repeated for all the questionnaires, except the one on the demographic variables. Indeed, as secondary analysis, differences in questionnaire scores between the two groups (i.e., HADS, Distress Thermometer, IES-R, Connor-Davidson Resilience Scale, the UCLA Loneliness Scale) will be assessed using the same analysis of the IES-R scale.

Group differences in questionnaires' measures will be analyzed with *T*-tests, while the chi-square statistic will be used to test the association between treatment groups and socio-demographic variables (gender, age, marital status, and employment status). Correlation analysis will be applied to assess the association between the questionnaires scores across all the time points.

Moreover, the scores of the HADS questionnaire will also be interpreted according to the clinical cutoffs (Annunziata et al., 2020). The scale score reliability (Cronbach α) will also be computed.

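### The sample size and ANOVA ignore the blended arm's three session groups; if outcomes within a group are correlated, type I error exceeds 5% and power falls below the stated 0.95

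*Protocol article*

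**What the plan says.** Under Participants and Procedure of the protocol article, participants are randomised individually, 75 per arm. Under Study Design and Measures, in the blended arm "participants will be split into three sub-samples of 25 persons", and once a week they "will be asked to participate in a 45 min group session with a psychotherapist". The same section explains that larger groups could reduce interaction among members and with the psychotherapist. The psychoeducational arm only receives links to fixed content.

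Under Sample Size Calculation and Statistical Analysis: "A repeated measure ANOVA will be performed to test differences in the IES-R total scores between groups across the four-time points". Time is the within-subjects factor and type of intervention the between-subjects factor; no other term is named. For the effect size, "the value of the F was set at 0.25". The other inputs are a two-sided alpha of 0.05, power of 0.95 and an assumed correlation of 0.5 between a participant's measurements. The result is 132, raised by 14% for attrition to 150. The same analysis is repeated for the secondary questionnaires. No ICC or design effect appears.

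The Discussion gives 31, not 25, as the planned size of a session group.

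**The concern.** People who meet weekly in the same interactive group may come to resemble one another in outcome, through the group's atmosphere, cohesion or attendance. If so, 75 blended participants carry less information than 75 independent ones, and the mean of that arm varies from trial to trial more than the spread between individuals suggests. An ANOVA without a session-group term does not see this extra variance. A difference could then reach significance because one of only three groups went unusually well or badly, and the stated power would not be delivered.

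This is not a detail left to an analysis plan. The protocol article itself fixes the model, its factors, alpha, power and sample size, and all of them rest on independence.

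**Working it through.** **1. Reproduce 132.** Inputs from the sample size section: f = 0.25, four measurements, correlation 0.5, alpha 0.05, power 0.95, two arms. For the between-groups F-test of a repeated measures ANOVA the noncentrality is f² × N × 4 / (1 + 3 × 0.5). At N = 132 this is 0.0625 × 132 × 4 / 2.5 = 13.2, with 1 and 130 degrees of freedom. Power is 0.9501; at N = 130 it is 0.9472. So 132 is reproduced exactly, with no allowance for clustering. The time-by-intervention version of the formula gives 36 and does not match. The step 132 × 1.14 = 150.5 is for attrition only.

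**2. Type I error with three groups of 25.** The documents give no ICC. I assume 0.01 to 0.05, with 0.10 as an upper bound.
- Design effect in the blended arm: DE = 1 + 24 × ICC.
- Effective blended-arm size: 75 / DE.
- Ratio of true to assumed standard error of the arm contrast: √((DE + 1)/2), because only one arm is clustered.
- True type I error: 2 × (1 − Φ(1.96 / ratio)).

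At ICC 0.05: DE = 2.20; ratio = √1.60 = 1.265; 1.96 / 1.265 = 1.55; type I error 12.1%.

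| ICC | DE | Effective size | SE ratio | Type I error, formula | Simulated two-sample test | Simulated ANOVA, between groups | Simulated ANOVA, time by intervention |
|---|---|---|---|---|---|---|---|
| 0.01 | 1.24 | 60 | 1.06 | 6.4% | 6.5% | 6.2% | 6.0% |
| 0.02 | 1.48 | 51 | 1.11 | 7.8% | 7.7% | 7.4% | 7.6% |
| 0.05 | 2.20 | 34 | 1.26 | 12.1% | 12.3% | 11.2% | 11.1% |
| 0.10 | 3.40 | 22 | 1.48 | 18.6% | 19.0% | 18.9% | 18.6% |

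The ANOVA columns (8,000 simulated trials per ICC) let the group effect arise after T0. At ICC 0 both ANOVA tests reject in about 5% of trials. If the group effect is instead equal at all four times, T0 included, the time-by-intervention test stays at about 5% and only the between-groups test is inflated.

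**3. Power at 132 (66 per arm, three groups of 22).** f = 0.25 corresponds to an arm difference of 2 × 0.25 = 0.5 SD. A participant's mean over four measurements has variance (1 + 3 × 0.5)/4 = 0.625. The variance of the contrast is vB + vC, with vB = 0.625 × (1 + 21 × ICC)/66 and vC = 0.625/66. The Satterthwaite df are (vB + vC)² / (vB²/2 + vC²/65), because three groups leave 2 df for the blended-arm mean.

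| ICC | Power, variance alone | Satterthwaite df | Power with those df |
|---|---|---|---|
| 0 | 95.3% | 7.8 | 88.5% |
| 0.01 | 93.3% | 6.5 | 83.2% |
| 0.02 | 91.0% | 5.7 | 77.7% |
| 0.05 | 83.7% | 4.4 | 62.7% |
| 0.10 | 71.8% | 3.5 | 45.6% |

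The variance-alone column is a normal approximation, hence 95.3% rather than 95.0% at ICC 0. With all 150 retained, power with Satterthwaite df is still only about 87%, 81%, 65% and 47% at ICC 0.01, 0.02, 0.05 and 0.10.

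**4. Can three groups estimate the ICC?** The group variance estimate is zero or negative when the between-to-within mean square ratio falls below 1. That has probability P(F with 2 and 72 df < (1 − ICC)/(1 + 24 × ICC)): about 48% at ICC 0.02 and 35% at ICC 0.05. A freely estimated random effect would then often reduce to the unadjusted analysis.

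**5. The other group size.** With 31 per group, DE at ICC 0.05 is 1 + 30 × 0.05 = 2.50 and the type I error about 13.8%. Three groups of 31 make 93, which does not fit an arm of 75, so group size and number are both unsettled.

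**The case against.** The strongest objection is that everything depends on an ICC the documents do not give. At ICC 0 there is no inflation, and at 0.01 to 0.02 it is moderate. That stands: a reader might infer that the type I error certainly exceeds 5%, and the documents do not support so flat a statement. Nor do they support 0.10 as a likely value. On one reading, the individual audio and video take 2 × (10 + 15) = 50 minutes a week against 45 in the group, which argues against a high ICC.

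A reader might also infer a therapist effect that differs between groups. The document speaks of a single psychotherapist and nowhere assigns different ones; if one person leads all three groups, that effect is common to the arm. Likewise, personal sharing is mentioned only as something that might be asked for, manageability is given as a reason for splitting, and fixed membership is implied rather than stated.

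The main endpoint concerns improvement, whereas 132 and the power losses above belong to the between-groups F-test. That also stands. The losses should not be read as the power of the time-by-intervention test, whose formula needs only 36 at the same nominal f. The type I error problem does reach that test when the group effect arises after baseline, which is when a group-delivered treatment would create one.

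The limitations in the Discussion do not answer the point: they treat group size as a matter of manageability and never mention independence.

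**Conclusion.** The point holds conditionally. The plan assumes exactly zero correlation within session groups without saying so, although its group size is partly meant to preserve interaction. For any positive post-baseline ICC the unadjusted test is too liberal: about 6.5%, 8% and 12% at 0.01, 0.02 and 0.05, and 19% at 0.10, in place of 5%. The 0.95 power at 132 holds for the between-groups F-test only under independence.

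These sizes rest on the assumed ICC range, three groups of equal size and, for the time-by-intervention test, a group effect that is absent at T0. The same analysis serves the secondary questionnaires, so they are exposed too. The primary test's error rate is at stake and group membership has to be captured during delivery, so this should be settled before the trial starts.

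**What to change.** - Record each blended-arm participant's session group, and reconcile 25 with 31 per group between Study Design and Measures and the Discussion.
- Replace the ANOVA with a partially nested mixed model: a session-group effect in the blended arm only, controls as singletons, and Satterthwaite or Kenward-Roger degrees of freedom. Report the estimated ICC.
- Because three groups often give a zero variance estimate, prespecify that the comparison is also reported with the ICC fixed at, for example, 0.01, 0.02 and 0.05. State that a zero estimate does not return the conclusion to the unadjusted ANOVA.
- Give power as conditional on a stated ICC in place of the unqualified 0.95, and say that the unadjusted test is relied on to hold 5% only at ICC 0.

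The cost is wider confidence intervals and a lower stated power; no participants or staff are added. The change does not restore 0.95. At 25 per group, before attrition and any df correction, that would take 132 × (DE + 1)/2, which is 148, 164 and 212 at ICC 0.01, 0.02 and 0.05. If the sponsor keeps 150, the lower figure should be stated openly.
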